### Outcomes: Domains, Tools, Measures, and Assessment Times

#### Overview

All outcomes reflecting the potential impacts of the intervention based on the logic model (see Figure 4) are prospectively collected at T_0_, T_1_, T_2_, and T_3_, except the participants’ satisfaction levels and perspectives and the endpoint interviews, which are only completed at T_2_. Outcomes are collected by a registered physiotherapist (AB) who has been trained with standardized data collection protocols adapted for WU_SCI_. All selected outcomes are commonly used in clinical trials targeting similar domains and populations—most have been used in the feasibility study—and most are summarized, including psychometric properties, and are recommended by well-established medical, rehabilitation, or psychosocial research organizations and networks [73]. A summary of all outcomes included in this study and the times at which they are administered is provided in Table 1. The following subsections describe all outcomes in detail.

**Figure 4 figure4:**
[figure not shown]
Project-specific logic model highlighting the relationships between the different domains of interest and related outcome measures. L/E: lower extremity; SCI: spinal cord injury; U/E: upper extremity; WRE: wearable robotic exoskeleton.

**Table 1 table1:** Summary of outcomes.

Outcomes			Measurement times^a^			
			T_0_	T_1_	T_2_	T_3_
**Clinical assessments**						
	**Personal characteristics**					
		Sociodemographic characteristics (age, sex, etc)	✓			
		Neurological impairment (American Spinal Injury Association Impairment Scale)	✓			
		Anthropometric parameters (weight and height)	✓			
		Resting heart rate and blood pressure	✓	✓	✓	✓
		Pain (International SCI [spinal cord injury] Pain Basic Dataset version 2.0)	✓	✓	✓	✓
		Passive range of motion at the ankle, knee, and hip joints (two-axis goniometer)	✓	✓	✓	✓
		Spasticity (Modified Ashworth Scale)	✓	✓	✓	✓
	**Wheelchair abilities**					
		20-meter wheelchair propulsion test (natural and maximal speeds)	✓	✓	✓	✓
		Slalom test	✓	✓	✓	✓
		6-minute manual wheelchair propulsion test	✓	✓	✓	✓
**Laboratory assessments**						
	**Bone mineral density and architecture**					
		Dual-energy x-ray absorptiometry (hip and lumbar vertebrae)	✓	✓	✓	✓
		Peripheral quantitative computed tomography (proximal tibia, distal femur, and proximal radius)	✓	✓	✓	✓
	**Body composition**					
		Dual-energy x-ray absorptiometry (total body)	✓	✓	✓	✓
	**Muscle quality**					
		Peripheral quantitative computed tomography (intramuscular fat infiltration)	✓	✓	✓	✓
	**Blood biomarkers**					
		Bone turnover (serum procollagen type 1 N-terminal peptide, osteocalcin, C-terminal cross-linking telopeptide, and 25-hydroxyvitamin D)	✓	✓	✓	✓
		Glycemia (fasting glucose, insulin, and glycosylated hemoglobin)	✓	✓	✓	✓
		Insulin resistance (homeostatic model assessment)	✓	✓	✓	✓
		Lipids (total cholesterol, high-density lipoprotein, low-density lipoprotein, triglycerides, and apolipoprotein B)	✓	✓	✓	✓
		Inflammation (C-reactive protein, tumor necrosis factor alpha, interleuken-6, and interleuken-10)	✓	✓	✓	✓
	**Cardiorespiratory fitness**					
		Respiratory gas analysis during 6-minute manual wheelchair propulsion test		✓	✓	
		Total distance travelled during the 6-minute manual wheelchair propulsion test	✓	✓	✓	✓
**Take-home assessments**						
	**Psychological health**					
		World Health Organization Quality of Life assessment	✓	✓	✓	✓
		Beck Depression Inventory	✓	✓	✓	✓
		Beck Anxiety Inventory	✓	✓	✓	✓
		Psychological General Well-Being Index	✓	✓	✓	✓
	**Participant satisfaction and perspectives**					
		Updated version of the Montreal Walking Exoskeleton Satisfaction and Perspectives Questionnaire			✓	
		Semistructured interview			✓	

^a^Measurement times: T_0_ (control measurement time), T_1_ (preintervention measurement time), T_2_ (postintervention measurement time), and T_3_ (retention measurement time).

#### Clinical Assessments

##### Personal Characteristics

Assessments are completed at the different assessment times to collect outcomes characterizing the following:

Sociodemographic characteristics (eg, age; sex; time since injury; history of fragility fracture; medications, including opioid analgesia, benzodiazepines, or unfractionated heparin; current smoking status; and alcohol intake) [74].Neurological impairment (eg, American Spinal Injury Association Impairment Scale for neurological level, motor and sensory scores, and severity) [75].Anthropometric parameters (eg, weight and height).Resting heart rate and systolic and diastolic blood pressure using an electronic sphygmomanometer machine [76].Pain using the *International SCI Pain Basic Dataset version 2.0*, which includes a set of core questions for up to three separate pain problems experienced over the past week and three questions on perceived pain interference with activities, mood, and sleep [77].Passive range of motion at the ankle, knee, and hip joints with a two-axis goniometer (ie, contracture).Upper extremity muscle strength (ie, pushing and pulling strength with a wheelchair wheel attached to an instrumented dynamometer and handgrip strength with a handheld dynamometer).Lower extremity spasticity using the *Modified Ashworth Scale* [78].

##### Wheelchair Abilities

Wheelchair abilities are assessed using the following performance-based wheelchair propulsion tests: (1) 20-meter wheelchair propulsion test (natural and maximal speeds), (2) slalom test, and (3) 6-minute manual wheelchair propulsion test [79-82]. The slalom test is used as a surrogate of trunk control since forward reaching distance is a good determinant (*r*=–0.75) [80] and trunk control is known to be the best predictor of multidirectional seated limits of stability during reaching (*R^2^*=0.95) [83]. The *Wheelchair Skills Test Questionnaire version 5.0* [84] is used as well to assess wheelchair abilities. This questionnaire assesses 34 wheelchair mobility and wheelchair-related skills. Each skill is rated on a 4-point self-reported scale: responses to the question *Can you do it?* include 0 (no), 1 (partially), 2 (yes), and 3 (very well). A capacity score is calculated (0%-100%), reflecting the number of skills that can be partially or completely done. Moreover, it assesses how confident—*How confident are you?* 0 (not at all), 1 (partly), 2 (moderately), or 3 (very)—and how often—*How often do you do it?* 0 (never), 1 (occasionally), 2 (usually), or 3 (always)—each skill is performed to calculate confidence and performance scores (0%-100%).

#### Laboratory Assessments

##### Bone Mineral Density and Architecture

A DXA system (Lunar Prodigy, GE Healthcare) is used to calculate aBMD at the hip, femoral neck, and the first to the fourth lumbar vertebrae [85]. Moreover, T-scores compare the measured aBMD values of each participant against values predicted from a matched reference group for sex, age, and ethnicity and are expressed as the number of SDs (ie, z scores or T-scores depending on age of participant). Measurements of aBMD and z scores or T-scores are directly provided by the system's software.

In addition, a peripheral quantitative computed tomography (pQCT) system (XCT 3000, Stratec Biomedical Systems) is used to characterize the volumetric bone mineral density (vBMD) and the microarchitecture parameters of trabecular and cortical bones at various imaging sites: 66% of the tibia, 25% of the femur, and 66% of the radius. These sites were chosen to maximize muscle circumference in each scan [86]. To minimize site-selection error between measurement times, images are taken using a standardized protocol including scout views with recommended reference lines [86]. As per current recommendations, reported pQCT outcomes will minimally include the following: total trabecular and cortical mineral content; cortical cross-sectional area and thickness; and biomechanical strength indices calculated from density and area (ie, bone strength indices, polar section modulus, and polar strength strain index) [86]. Outcomes are calculated using a validated open source image analysis software package (Fiji distribution of ImageJ) [87,88].

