### Participants and Inclusion and Exclusion Criteria

We aim to recruit a nonprobabilistic consecutive sample of 20 long-term WU_SCI_. The inclusion and exclusion criteria are listed in Textbox 1. Initial screening is conducted by phone to establish eligibility based on criteria developed during the feasibility study. Once deemed eligible from the initial clinical screening, potential participants attend a short assessment to confirm eligibility.

Inclusion and exclusion criteria.Participant-specific inclusion criteria:Adults (≥18 years old)Chronic complete or incomplete traumatic or nontraumatic spinal cord injury (SCI) at least 18 months before enrollmentLong-term manual wheelchair use as primary means for in-house and community mobility (ie, nonambulatory)Understand and communicate in English or FrenchReside or will arrange for temporary housing in the community within 75 km from the main research siteParticipant-specific exclusion criteria:Other neurological impairments aside from those linked to the SCI (eg, multiple sclerosis)Concomitant or secondary musculoskeletal impairments (eg, hip heterotopic ossification)History of lower extremity fracture within the past yearUnstable cardiovascular or autonomic systemRenal insufficiencyPregnancyAny other conditions that may preclude lower extremity weight-bearing, walking, or exercise tolerance in the wearable robotic exoskeletonExoskeleton-specific inclusion criteria:Body mass: ≤100 kgHeight: 1.52-1.93 mPelvis width: 30-46 cmThigh length: 51.0-61.4 cmLower leg length: 48.0-63.4 cmExoskeleton-specific exclusion criteria:Inability to sit with hips and knees at ≥90° flexionLower extremity passive range of motion limitations (hip flexion contracture ≥5°, knee flexion contracture ≥10°, and ankle dorsiflexion ≤–5° with knee fully extended)Moderate-to-severe lower extremity spasticity (score of >3 on the Modified Ashworth Scale)Length discrepancy (≥1.3 cm or ≥1.9 cm at the thigh or lower leg segment, respectively)Skin integrity issues preventing wear of the wearable robotic exoskeleton

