**Figure 3 figure3:**
[figure not shown]
Progression of the number of training sessions per week during the 16-week walking program.

Total hip areal bone mineral density (aBMD), determined with dual-energy x-ray absorptiometry (DXA) scans performed at T_1_, is used to assign each participant to one of three training regimes based on lower extremity fracture risks [69]: (1) conservative (T-score ≤ –2.5; first session includes a maximum of 300 steps; number of steps progresses up to 10% every week), (2) moderate (–2.5 < T-score < –1.0; first session includes a maximum of 400 steps; number of steps progresses up to 15% every week), or (3) aggressive (T-score ≥ –1.0; first session includes a maximum of 500 steps; number of steps progresses up to 20% every week). Workload is further individualized depending on each participant’s level of proficiency and tolerance; it is progressively and safely increased by modifying walking parameters (eg, number of steps, speed, and duration) or reducing total resting time or level of assistance provided by the physiotherapist to maintain a moderate-to-vigorous training intensity (ie, rate of perceived exertion ≥3/10 on the Modified Borg Scale [70]). Training parameters are recorded at the end of each session (eg, total standing time, total walking time, total number of steps, assistance provided, and rate of perceived exertion). Given the risks of adverse events inherently linked to the use of a wearable robotic exoskeleton [69,71], skin integrity at interface pressure points, particularly at the tibial tuberosity, and signs of inflammation at the ankle and knee joints before and after each training session, respectively, are assessed and any serious adverse events will be reported.

To be considered as having successfully completed the program, at least 75% of the training sessions (ie, 26/34) need to have been completed. To this effect, to assure an optimal attendance rate similar to the one reached during the feasibility study (ie, attendance rate was 97.7%) [72] and to overcome one of the most commonly reported barriers to intervention studies (ie, transportation), participants have three key options: (1) driving their own car or being transported by car by a family member or a friend with free parking provided within 50 meters from the entrance, (2) using public transit, or (3) scheduling trips with the adapted transport free services.

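### The T-score is defined as an age-matched score (a z score), yet the fracture-risk loading regimes are set by cut-offs stated only for the T-score

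*Protocol article*

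**What the plan says.** The protocol article defines the score once, under Laboratory Assessments, Bone Mineral Density and Architecture. T-scores are said to compare measured areal bone mineral density (aBMD) "against values predicted from a matched reference group for sex, age, and ethnicity", and the result is given in SDs as "z scores or T-scores depending on age of participant". No age threshold for the choice is stated. The paragraph then adds: "Measurements of aBMD and z scores or T-scores are directly provided by the system's software".

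The score is used in the Intervention section, in the paragraph after Figure 3. Total hip aBMD from the DXA scan at T1 "is used to assign each participant to one of three training regimes based on lower extremity fracture risks". The three bands are:

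- conservative: T-score of –2.5 or lower; "first session includes a maximum of 300 steps" and "number of steps progresses up to 10% every week";
- moderate: T-score between –2.5 and –1.0; at most 400 steps at first, then at most 15% more each week;
- aggressive: T-score of –1.0 or higher; at most 500 steps at first, then at most 20% more each week.

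The eligibility criteria admit adults from 18 years with no upper age limit.

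**The concern.** By standard densitometry terms, a score against an age-matched group is a z score, and a T-score is measured against young adults. The article gives the first meaning to the second name, and then treats the two as alternatives chosen by age. The regime rule, however, has bands for the T-score alone.

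Taken together, the two sections allow two misreadings. A member of staff could place an age-matched value in the T-score bands. Or a participant whose report shows a z score could be left with no applicable cut-off.

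The first matters more, because the rule exists to limit loading in people at risk of lower extremity fracture. Mean bone density falls with age in later adulthood, so an age-matched score tends to be higher (less negative) than the T-score. A participant just below a cut-off would then be moved to a heavier regime than the rule intends. A reader of the published DXA scores also could not tell which reference group was used.

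**Working it through.** There is no stated power, sample size or error rate to reproduce on this point. The check compares the two sections and then sizes what one step in regime means.

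**Comparison of the two sections**

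| Item | Bone Mineral Density and Architecture | Intervention, after Figure 3 |
|---|---|---|
| Name of score | z score or T-score, by age | T-score only |
| Reference group | matched for sex, age and ethnicity | not stated |
| Cut-offs | none | –2.5 and –1.0 |
| Applies to | each participant | each participant |

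Nothing elsewhere in the article corrects the definition or gives a z-score band.

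**Direction of a possible error**

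Let d be the number of SDs by which the age-expected mean lies below the young-adult mean. With equal SDs, z = T + d. The article does not give d; I take 0 to 1.0 as an assumed range.

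- d = 0 (a young adult): z = T, and the regime does not change.
- d = 0.25: T = –2.5 (conservative) gives z = –2.25 (moderate); T = –1.2 (moderate) gives z = –0.95 (aggressive).
- d = 0.5: T = –1.5 (moderate) gives z = –1.0 (aggressive); T = –3.0 gives z = –2.5 and stays conservative.
- d = 1.0: T = –3.0 (conservative) gives z = –2.0 (moderate).

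For any d above 0, a change of regime is always towards more loading. I have not estimated how many of the 20 participants would move. That needs the age distribution, the T-score distribution, d, and knowledge of which score staff used, and none of these is in the article.

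**Size of one step in regime**

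Inputs, all from the Intervention section: starting maxima s = 300, 400, 500 and weekly limits g = 10%, 15%, 20%. Let k be the number of weekly increases, so that week 8 is k = 7. The article does not say whether increases compound, so both readings are shown, each using the full permitted percentage every week.

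First session (k = 0): 400/300 = 1.33 and 500/400 = 1.25.

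Compounding, s × (1 + g)^k:
- 300 × 1.10^7 = 585
- 400 × 1.15^7 = 1,064
- 500 × 1.20^7 = 1,792
- ratios: 1,064/585 = 1.82 and 1,792/1,064 = 1.68

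Taken on the starting value, s × (1 + g × k):
- 300 × (1 + 0.10 × 7) = 510
- 400 × (1 + 0.15 × 7) = 820
- 500 × (1 + 0.20 × 7) = 1,200
- ratios: 820/510 = 1.61 and 1,200/820 = 1.46

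These are permitted ceilings, not doses delivered.

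**The case against.** The best reply is that the operative rule is clear. The Intervention section names the T-score in all three bands and mentions neither a z score nor a switch by age. The paragraph with the faulty definition describes outcome measures, and the scores come from the DXA software, so nobody computes one from the article's wording. If staff read the software's T-score for everyone, every assignment is right and only the prose is wrong.

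Second, harm needs two things that tend not to occur together. If the choice by age means z scores for younger adults, those who get a z score are mostly those in whom the two scores nearly coincide, while older participants, in whom the gap is larger, get the T-score.

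Third, the step figures are ceilings within a supervised program. "Workload is further individualized depending on each" participant's proficiency and tolerance, a physiotherapist supervises every session, skin and joints are checked around each session, and a lower extremity fracture in the past year is an exclusion.

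Finally, this is a journal article, and a fuller protocol or training manual may spell out the assignment procedure.

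Most of this stands, and it is why the point is minor. It does not remove the point. The article chose to define the score and defined it incorrectly, which is different from leaving a detail to a fuller document. The reading in which only younger adults get a z score is plausible, but the text does not state it and gives no age threshold. A modest gap in middle-aged participants cannot be excluded.

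**Conclusion.** The concern holds, at minor severity. The definition of the T-score is wrong as written, and it conflicts with a dosing rule that has cut-offs for the T-score only. Confidence is high for that and low that any participant was placed in the wrong regime.

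The consequence is conditional on two things: an age-matched score being used for assignment, and that score lying above a cut-off that the T-score does not reach. For a participant so affected, the first-session ceiling is 33% or 25% too high. By week 8 the ceiling is about 1.5 to 1.8 times the intended one, depending on the pair of regimes and on whether increases compound. The number affected may be zero or few.

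Sample size, error rates, the measurement of total steps, and the aBMD and pQCT outcome values do not depend on this.

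**What to change.** - **Intervention section:** add one sentence saying that regime assignment uses the total hip T-score against the young-adult reference for every participant, whatever their age.
- **Bone Mineral Density and Architecture:** correct one sentence so that T-score means the comparison with young adults and z score the comparison with an age-matched group, with z scores reported descriptively only.
- **Participants already assigned:** check their existing DXA printouts to confirm that the T-score was the value used.

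The cost is two sentences and a review of printouts. No new scans are needed, and the change agrees with the rule that the Intervention section already states.

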##### Body Composition

Whole-body scans obtained with the DXA system are used to quantify total and regional (ie*,* upper extremities, trunk, and lower extremities) body fat and fat-free (ie, lean) tissue mass and relative percentages, respectively [89]. These measures are directly provided by the DXA system's software.

##### Muscle Quality

Cross-sectional images of the femur, tibia, and radius captured with the pQCT system are also used to measure the muscle size (ie, cross-sectional area) and intramuscular fat infiltration (ie, muscle density) using the same validated open source image analysis software [87,88].

##### Blood Biomarkers

Fasting blood samples (ie, >8-hour fast) are used to quantify bone turnover biomarkers (ie, serum procollagen type 1 N-terminal peptide, osteocalcin, C-terminal cross-linking telopeptide, and 25-hydroxyvitamin D), glycemic biomarkers (ie, fasting glucose, insulin, and glycosylated hemoglobin), insulin resistance biomarkers (ie, homeostatic model assessment), lipid biomarkers (ie, total cholesterol, high-density lipoprotein, low-density lipoprotein, triglycerides, and apolipoprotein B), and inflammatory biomarkers (ie, C-reactive protein, tumor necrosis factor alpha, interleuken-6, and interleuken-10).

##### Cardiorespiratory Fitness

At T_1_ and T_2_, participants complete the 6-minute manual wheelchair propulsion test wearing a gas analyzer system (COSMED K4b2, COSMED srl). This portable system incorporates a sealed face mask placed over the mouth and nose and anchored around the head, a telemetric stationary O_2_ and CO_2_ gas analyzing unit, and a battery harnessed to the anterior and posterior thorax. This system is calibrated before each test as recommended by the manufacturer. For the other two measurement times (ie, T_0_ and T_3_), the total distance travelled during the 6-minute manual wheelchair propulsion test is used as a surrogate measure of cardiorespiratory fitness since it has been found to strongly correlate and agree with the maximal arm-crank test (*r*=0.92; mean difference 0.21 ±1.94 mL/kg·min) [90].

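### The 6-minute propulsion test appears to be run with a gas-analysis mask and harness at T1 and T2 only, so the T0–T1 and T2–T3 changes in distance mix equipment with time

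*Protocol article*

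**What the plan says.** The Cardiorespiratory Fitness section states the test condition for two visits: "At T_1_ and T_2_, participants complete the 6-minute manual wheelchair propulsion test wearing a gas analyzer system". It describes the equipment: "This portable system incorporates a sealed face mask placed over the mouth and nose and anchored around the head", with an analysing unit and battery harnessed to the chest. For T0 and T3 it says that "the total distance travelled during the 6-minute manual wheelchair propulsion test is used as a surrogate measure of cardiorespiratory fitness".

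Table 1 matches this. The row "Respiratory gas analysis during 6-minute manual wheelchair propulsion test" is ticked at two times. The row "Total distance travelled during the 6-minute manual wheelchair propulsion test" is ticked at all four, and so is the same test where it appears as a wheelchair-ability outcome.

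The Outcomes Overview is broader. It begins "All outcomes reflecting the potential impacts of the intervention based on the logic model" and says these are collected at T0, T1, T2 and T3, excepting only satisfaction, perspectives and the interviews.

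The Quantitative and Qualitative Analyses section plans a repeated-measures analysis over time, with special interest in T0 vs T1, T1 vs T2 and T2 vs T3. Study Design uses the four weeks from T0 to T1 to measure each participant's natural variability and to derive a patient-specific minimal detectable change. Hypothesis 1 requires the later effects to exceed the changes seen before the program.

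**The concern.** The trial has no comparison group, so the T0–T1 phase is its only control. For that phase to measure natural variability, the test has to be run in the same way at both ends. For propulsion distance it apparently is not: equipment is added between T0 and T1 and removed between T2 and T3. Within each of those phases, equipment and time change together in every participant, and no later analysis can separate them.

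Two of the three planned phase contrasts for distance are affected, together with the benchmark against which the program's effect is to be judged. Distance also serves as the stand-in for cardiorespiratory fitness at T0 and T3, so the control and retention statements about fitness rest on the same contrasts.

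A smaller point goes with it. Gas exchange is measured only at T1 and T2, so it has no control-phase or retention comparison, although the Overview's wording implies that it does.

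**Working it through.** The plan states no figure for this point, so there is nothing to reproduce. The check is contrast algebra followed by an illustration of size.

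**Inputs from the article.** Planned sample of 20 (Participants). Significance level 0.05 with Bonferroni correction, and three contrasts of special interest (Quantitative and Qualitative Analyses). Equipment at T1 and T2, none at T0 and T3 (Cardiorespiratory Fitness and Table 1, natural reading).

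**Assumptions.** The Bonferroni divisor is taken as 3, so alpha = 0.05/3 = 0.0167. The equipment effect e is the same for everyone and is expressed in SDs of the within-person change between two visits. All 20 participants contribute. The documents give no value for e or for that SD.

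**Algebra.** Suppose nothing truly changes and the equipment shortens distance by e. Expected distances at T0, T1, T2, T3 are m, m – e, m – e, m.

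- T0 to T1: (m – e) – m = –e
- T1 to T2: (m – e) – (m – e) = 0
- T2 to T3: m – (m – e) = +e
- Program change minus control-phase change: 0 – (–e) = +e

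If the equipment lengthened distance, every sign would reverse. In either case the four visit means differ without any true change, so the omnibus time test is affected too.

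**Size.** For a paired t test with n = 20, the noncentrality is e × √20 and the two-sided critical value on 19 degrees of freedom is 2.625. The false-positive rate for T0 vs T1, and equally for T2 vs T3, is:

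| e (SD of change) | noncentrality | false-positive rate |
|---|---|---|
| 0 | 0 | 1.7% |
| 0.1 | 0.447 | 2.6% |
| 0.2 | 0.894 | 6% |
| 0.4 | 1.789 | 23% |
| 0.5 | 2.236 | 37% |
| 1.0 | 4.472 | 96% |

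A simulation of 20,000 trials, with independent errors at each visit, agrees: about 37% at 0.5 SD and 96% at 1.0 SD for both affected contrasts, while T1 vs T2 stays at 1.6%–1.8%. In the same simulation, a test of program change against control-phase change rejects in about 12% of trials at 0.5 SD and 50% at 1.0 SD. With one condition at every visit (e = 0), all contrasts return to 1.5%–1.8%.

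**The case against.** **A separate run may exist.** Table 1 lists the propulsion test under clinical assessments and the gas analysis under laboratory assessments, and two laboratories take part. A run without equipment at T1 and T2 is therefore possible, and an article may leave such detail to the full protocol. This stands as a possibility. It is not the natural reading: no section describes a second run, and T0 and T3 are set apart as the visits where distance takes the place of gas analysis. If a second run is done, one sentence would settle the point.

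**Direction.** A reader might infer that the artefact flatters the program, since a hindering mask would give a false decline before it and a false gain after it. The documents do not support this. They do not say that the equipment slows propulsion. Even if it does, a patient-specific minimal detectable change built on the size of the T0–T1 difference would be inflated by the shift, which works against Hypothesis 1.

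**Size.** The rates depend entirely on the assumed ratio of e to the SD of change. At 0.1 to 0.2 SD they are only 2.6% to 6%. This is correct, and the table should be read only as an illustration.

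**The surrogate.** A reader might also infer that the cited agreement, "mean difference 0.21 ±1.94 mL/kg·min", cannot support distance as a surrogate because it is in units of oxygen uptake. That goes too far. What was compared depends on a source not shown here, and the article also cites a correlation of 0.92, which can link measures in different units.

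**Gas exchange.** The two-visit schedule is openly stated in the section and in Table 1. The Overview's missing exception is a wording slip, not a hidden design flaw.

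**Conclusion.** The point holds for distance in the 6-minute test. As the article is naturally read, T0 vs T1 and T2 vs T3 cross a change in test condition, so the control-phase benchmark, the retention contrast and the four-time omnibus test all carry any equipment effect. This follows from the schedule. The size and direction of the effect are unknown, and the illustrated false-positive rates, from near nominal to 96%, rest on assumed values.

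Two limits apply. The direct pre-post contrast, T1 vs T2, is made under one condition and is sound in this respect. And the article names body composition and bone mineral density as the main outcomes, so neither they nor the sample size is touched. The matter deserves correction because the remedy is cheap and because the control phase is what this design offers in place of a comparison group.

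**What to change.** Measure distance under one equipment condition at all four visits, for example by having participants wear the same mask and harness at T0 and T3 without needing the gas data. The cost is a slight extra burden at two visits. If a run without equipment already takes place at T1 and T2, say so and name it as the source of the distance outcome.

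If the visits cannot be changed:

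- restrict inference on distance to T1 vs T2;
- report T0 vs T3 only as a descriptive comparison under the same condition. It spans the control, program and follow-up phases and cannot show that a gain at T2 was kept;
- make no control-phase, T2–T3 or four-time omnibus claim for distance.

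This second route costs only wording, but it leaves distance with no control-phase estimate, and the article should say so.

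In either case, state that gas-exchange outcomes are pre-post only, and add them to the exceptions in the Outcomes Overview so that it agrees with Table 1.
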